## ABSTRACT

This research has been registered in <http://www.clinicaltrials.gov/> under the n° NCT06379698

Effects of a personalized or generic three-dimensional tumoral kidney model on patient experience and professional-patient interactions, before and after partial nephrectomy. R3DP-P

The University Hospital of Bordeaux is the sponsor of this research.

This research will be conducted with the support of ANR-21-RHUS-0015.

**Brief summary:** We aim to compare preoperative information and patient experience using a personalized versus a generic 3D printed models of patients' tumoral kidney before and after nephron-sparing surgery. The main outcome measure will be based on semi-structured interviews with the patient and the carers.

**Detailed description:** Use of tools to decrease anxiety and enhance understanding prior to surgery is a key point in comprehensive care that is way not enough promoted for now.

A pilot study from 2015 demonstrated the benefits of using personalized 3D-printed kidney models as educational mediation tools during the pre-operative consultation of patients scheduled for robot-assisted partial nephrectomy. The patient's understanding of his pathology and of the surgery was thus facilitated, leading to greater satisfaction during treatment.

For personalized medicine, it is important to consider the heterogeneity in culture and social backgrounds of patients in the doctor-patient relationship. Measuring health literacy help to identify and describe this heterogeneity in patient profiles. Patients with low literacy levels have higher levels of anxiety, particularly regarding surgery, and poorer post-operative recovery. Some studies highlight the importance of improving patient understanding with strategies to improve patients' health literacy and information provided by carers.

The aim of this study is therefore to investigate the benefits of using a personalized 3D-printed kidney model versus a generic 3D-printed kidney model as a mediation tool, all along the care pathway, on patients' experience and their interactions with carers, before and after partial nephrectomy.

To achieve this aim, 60 patients planned for robot-assisted laparoscopic partial nephrectomy will be randomized, in a 1:1 ratio, between the use of a personalized 3D kidney model and a generic 3D kidney model.

3D models will be presented to the patients according to the allocated study group during a preoperative education consultation. All patients will complete questionnaires about their health literacy level, their knowledge of kidney anatomy and tumor and their satisfaction about the using 3D-printed kidney models as educational mediation tools. Semi-structured interviews will be conducted at three different times: between the first consultation with the surgeon and the preoperative education consultation, between this second consultation and the surgery and after the post-operative consultation.

Primary outcome:

To study the effects of using a personalized versus a generic 3D-printed kidney model as a mediation tool on patients' experience and interactions with carers, before and after partial nephrectomy.

This is a mixed-type study designed to combine data from different collection tools (observations, interviews and questionnaires). The criteria studied are:

For the patient:

- Qualitative assessment of the patient experience
- Changes in the average score of the HLSEU-Q16 literacy questionnaire - Level of understanding of renal anatomy and of the surgical issues

For the carers:

- Qualitative assessment of changes in practice following the integration of 3D models into the department

Secondary outcomes:

1. Description of interactions between carers and patients, specifying the situations and the environments, the practice, vocabulary and content of the discourse used during the entire care process.
2. Comparison of the differences in speech and terminology used when using the different tools during interactions between patients, carers and patients' entourage with systematic analysis of interviews.
3. Studying the use of the 3D-printed kidney model introduced during the medical information consultation up to the post-operative visit by describing the life of the model throughout the entire care process (from the inclusion visit to the post-op visit).
4. Comparison of the patient's understanding of anatomy and surgical strategy according to the type of tool (personalized vs generic 3D printed model) before and after the surgery (T1, T3 and T6).
5. Comparison of the level of health literacy between the two groups at different times with changes in the average score on the literacy questionnaire (HLSEU-Q16: European Health Literacy Survey Questionnaire; T1 and T6).
6. Description of the changes perceived by carers in patients management following the integration of the mediation tool with patients by qualitatively assessing changes in practices following the integration of 3D models during the entire care process.

Study design: Monocentric, randomized and controlled clinical trial Eligibility criteria:

- Patients:

- Adult patients ( $\geq 18$  years of age)
  - Scheduled for surgical management by laparoscopic robotic-assisted partial nephrectomy (1st management for a unilateral or bilateral kidney tumor)
  - Expressed consent for integration in the UroCCR database
  - Expressed consent for participation in the Rein-3D Personalize study
  - Patients affiliated or benefiting from social security system
- Carers:
    - Carers working with patients treated in the Urology, Andrology and Renal Transplant Department of the Bordeaux University Hospital for at least two months prior to the implementation of 3D models
    - Free, informed and signed consent

Arm number or label and arm type:

- Group 1: 3D Printed Personalized Model Group: exchange time with the printed threedimensional model of the patient's kidney as information support.
- Group 2: 3D Printed Generic Model Group: exchange time with the printed threedimensional generic kidney model, approximating the patient's situation, as information support.

Number of subjects: 60 patients and 30 carers -

#### Statistical analysis :

A mixed analysis of the data will be realised with a triangulation approach. The sociodemographic data and the medical profiles of the patients will be described (in terms of frequencies for the qualitative data and with means and standard deviations for the quantitative data) and will be compared between the two groups. Data from patients questionnaires will be analysed descriptively (distribution of patient scores for the HLS-EU16 literacy questionnaire at start and end and at the end distribution of satisfaction with use of the 3D model.). The analysis of the patients' experience will be based on the content of the cross-sectional interviews at each stage, but also on a longitudinal analysis. The evolution of the understanding of the disease and the surgery will be studied by analysing the content of the interviews and questionnaires and a comparison between the two groups will be made.

Content of the carers interviews will also be analysed.

Conditions: kidney cancer surgery

Keywords: Renal-Cell Carcinoma, Nephron-Sparing Surgery, 3D Model, 3D Printing, Personalized Medicine, Literacy Questionnaire, Interviews.

## **1. SCIENTIFIC JUSTIFICATION AND GENERAL DESCRIPTION**

## 1.1 CURRENT STATE OF KNOWLEDGE

In 2015, a pilot study evaluated the use of a personalised 3D-printed kidney model in 7 English-speaking patients who were being considered for partial nephrectomy (1). It was shown that these 3D models could be used as educational mediation tools to make it easier for patients to understand their pathology and surgical management.

Better communication would give patients a better understanding of the issues involved in surgery and give them greater satisfaction with the course of their visits and medical follow-up (2).

However, as the study by Curchod et al. points out, ‘the care provided in our society is aimed at people from diverse and varied cultures and social backgrounds’ (3). It is therefore essential to take account of this heterogeneity in the care-giver-patient relationship, thus defining the notion of personalised medicine. Health literacy, defined by the WHO as ‘the cognitive and social skills that determine people's motivation and ability to obtain, understand and use information in ways that promote and maintain good health’, makes it possible to identify and describe this heterogeneity in patient profiles.

According to a study by the DREES (Direction de la recherche, des études, de l'évaluation et des statistiques), published in May 2023, 10.7% of the population consider that they have difficulty understanding medical information (4). In the case of surgery, it has been shown that patients with a low level of literacy have a higher level of anxiety (5), particularly in relation to the operation (6), and a poorer level of post-operative recovery (7). Numerous studies have been carried out to develop strategies for improving the health literacy of cancer patients and information methods for carers (8-10). They emphasise the importance of improving understanding of the information given to patients.

A patient diagnosed with a kidney tumour will meet a number of different healthcare professionals during his or her hospital stay. The interactions that will take place between the patient and each professional will depend on the place, the context, the patient's personal characteristics (age, gender, profession, literacy level, etc.) and also the various conceptions that the professional has of the patient as a subject. For example, if the patient is seen as a player in his or her own care, i.e. able to acquire and develop care skills through the professional-patient relationship, then professionals' expectations of the patient and his or her interpersonal skills will be high (11).

The introduction of new technologies into patient care can therefore change the way professionals behave (12). For example, the use of a 3D-printed kidney model can change the patient's understanding of his pathology and its management, as well as his interactions with all the professionals involved.

In 2022, the study by Scott et al, based on a protocol similar to that of Bernhard et al (1) and using the same comprehension questionnaire, confirmed the impact of these personalised models on patient comprehension, while highlighting the financial impact of their manufacture (13). The study by Bernhard et al. used personalised 3D printed models, i.e. a reproduction of the patient's kidney made from the preoperative scan (1). However, the cost and time taken to produce these models may make it difficult to incorporate them into clinical practice during the preoperative consultation. It therefore seems worthwhile evaluating the use of different models that are not personalised but represent the different tumour situations that are classically found.

The addition of a specific pre-operative information consultation, using a personalised or generic 3D printed model of the kidney, can have a different impact (depending on the model) on the patient's experience, their level of literacy and their interactions with healthcare professionals.

This study is part of the RHU Digital Urology 3D programme, which includes several studies aimed at assessing the contribution of 3D models in patients undergoing robot-assisted laparoscopic partial nephrectomy (e.g. the ANXIETY study conducted by Bordeaux University Hospital, NCT06035211). The Rein 3D Print-Personalize (R3DP-P) study will evaluate the information situations throughout the patient's care in the Urology department, depending on the type of model used during the pre-operative information consultation (generic or personalised), using an anthropological approach.

## 1.2. RESEARCH HYPOTHESES AND EXPECTED RESULTS

The R3DP-P study evaluates the personalised aspect of the 3D-printed tool, its interest for the patient (diagnosis of a renal tumour accessible to conservative surgical treatment) and its impact on his understanding of the disease and its management, as well as on his relations with healthcare professionals.

The main hypothesis is that the personalised aspect of the 3D-printed model leads to the use of the model as a mediation tool during the patient's social interactions with family and friends and with healthcare professionals to discuss the disease, or during the development of knowledge. This use would reflect an appropriation of the personalised 3D model. In addition, it is assumed that the patient's observation and manipulation of the 3D representation of 'their' kidney would enable them to better understand their pathology throughout the care pathway.

The R3DP-P study is based on a didactic health anthropology approach, where the reflexivity of the principal investigator and the field are the driving force behind the scientific method. The working hypotheses are as follows:

- Hypothesis 1: The 3D-printed personalised kidney model enables patients to 'better' understand their pathology and the surgical procedure.
- Hypothesis 2: The 3D-printed personalised kidney model makes it easier for patients to communicate with their family and friends about their condition.
- Hypothesis 3: The 3D printed personalised kidney model improves the therapeutic alliance between patients and professionals.
- Hypothesis 4: The 3D-printed personalised kidney model leads to a change in professionals' information practices.

## 1.3. JUSTIFICATION FOR THE LOW LEVEL OF INTERVENTION

The nature of the R3DP-P study does not involve any risks and is associated with minimal constraints for patients.

This research does not entail any change in the patient's indications and clinical management strategies, as validated by the surgical team in accordance with current recommendations and the conclusions of the multidisciplinary consultation meeting (RCP).

Only one preoperative information consultation will be added to the patient's conventional care, 7 to 30 days before the operation, delivered by a doctor: this will be a specific time, mediated by a 3D printed model, dedicated to informing the patient.

As for the professionals who have agreed to take part, the interviews will be conducted by the SHS researchers at their convenience and in the place of their choice, in order to make it easier for them to talk, not to interfere with their care and not to disrupt their daily lives.

The research method is based on interviews, questionnaires to understand the pathology and observations. If, during an interview with a patient or a professional, a researcher notes a need for psychological support, she will refer the participant to a healthcare professional. The SHS researchers will act as observers to understand the different situations of interaction between patients and professionals and will ensure that they never disrupt the situations (particularly consultations). An oral request will always be made to obtain the agreement of the protagonists in the situation being observed.

#### 1.4. RISK/REWARD RATIO

The main expected benefit is improved understanding of preoperative information, an essential condition for better preparation before surgery.

##### Patients

The addition of a mediated consultation to the care pathway can also be seen as a benefit, as it gives patients the opportunity to ask all their questions before the operation. It does, however, oblige the patient to return to the care centre for an additional period of time.

As the study intervention consists of taking part in research interviews and answering (non-diagnostic) questionnaires, there is no physical risk during participation.

Nevertheless, it is possible that asking questions related to the presence of renal tumours could lead to other questions being asked. Indeed, the questions question the patient's feelings. It is conceivable that the patient will then begin a process of introspection that he or she had not experienced before, which may have psychological consequences that are considered to be moderate. It should be emphasised that the patient's overall care is part of a care network that includes close nursing support and contacts (particularly psychologists) available throughout the patient's follow-up.

##### Professionals

The R3DP-P study protocol is qualitative and non-interventional, based on observations and interviews with no expected effect on professionals or patient management.

#### 1.5. EXPECTED BENEFITS

The expected outcomes of the R3DP-P mixed (qualitative and quantitative) study are :

- For patients
  - o Acquire knowledge on the contribution of the materialization of the pathology in its understanding.
  - o Evaluate the appropriation of the 3D tool as a mediation and comprehension (literacy) tool by patients.
  - o To improve patients' experience of hospitalisation and surgery.
- For professionals
  - o To assess the appropriation of the 3D tool as a mediation tool by professionals.
- For the healthcare system :
  - o Identify specific uses depending on whether or not the model is personalised, and assess the benefits of personalising the 3D tool and the value of implementing it in everyday practice.

## 2. RESEARCH OBJECTIVES

### 2.1. MAIN OBJECTIVE

To use qualitative studies to investigate the effects of using a personalised 3D-printed kidney model versus a generic 3D-printed kidney model as a mediation tool, throughout the care pathway, on patients' experience and their interactions with professionals, before and after partial nephrectomy.

### 2.2. SECONDARY OBJECTIVES

1. To use qualitative studies to describe interactions between professionals and patients, specifying the situations in which exchanges take place and their environments.
2. To use qualitative studies to analyse differences in discourse and the use of terms in the use of different tools during interactions between patients, professionals and their families.
3. To use a qualitative approach to study the use of the 3D-printed kidney model introduced during a medical information consultation right through to the post-operative visit.
4. To compare patient understanding of anatomy and surgical strategy according to the type of tool, personalised or generic, before and after the operation on the basis of questionnaires and interviews.
5. To compare the level of health literacy between the two groups and at different times (HLSEU-Q16: European Health Literacy Survey Questionnaire).
6. To use qualitative studies to describe the changes perceived by professionals in patient care following the integration of the mediation tool with patients. In order to meet the objectives set out above, the study will focus on two populations: patients and professionals.

### 3. ASSESSMENT CRITERIA

#### 3.1. MAIN ASSESSMENT CRITERIA

##### Qualitative assessment of the patient experience

This is not a single criterion, but a set of elements used to describe the patient experience based on the interviews. Observations and the three questionnaires used (literacy, knowledge and satisfaction questionnaires: appendices 1, 2 and 3) complete the analyses of the qualitative data. The patient experience collected will also be analysed in relation to the clinical and demographic data from the UroCCR database.

#### 3.2. SECONDARY ASSESSMENT CRITERIA

Course of interactions between professionals and patients: description of the course of interactions according to the model used, specifying the practice as well as the vocabulary and content of the discourse used.

Frequency of terms used in accordance with the use of the different tools during interactions: comparison of the differences in discourse and terminology when using the different tools

during interactions between patients, carers and the patient's entourage with the systematic analysis of the interviews.

Use of the 3D model during care: description of the life of the model throughout care (from the inclusion visit to the post-operative visit).

Level of understanding of renal anatomy and surgical issues measured using the translation of the questionnaire proposed by Bernhard et al (1) (appendix 2). This questionnaire consists of 4 parts: physiological and anatomical dimensions, knowledge of the disease and tumour characteristics, understanding of the surgical procedure and associated risks of complication. These dimensions will be studied before and after the presentation of the model and compared according to the model used. The final part of the questionnaire, based on the evaluation of patient satisfaction, will be presented at the end of the post-operative consultation period (T6) (Appendix 3).

Evolution of the mean score of the HLSEU-Q16 literacy questionnaire measured (health literacy)

The evolution of the literacy score according to the type of mediation tool used during the information consultation will be assessed by measuring the HLSEU-Q16 at inclusion and 1 month post-operatively. This questionnaire is based on a model including four skills related to the processing of health information: access, understanding, evaluation and application of health information (Appendix 1). These four skills are explored in three health contexts: health care, disease prevention and health promotion. The HLSEU-Q16 is composed of 16 items. All dimensions are explored except for the dimension “applying information in health promotion”. This short version was validated in French by Rouquette et al. in 2018 (15). Each item is rated on a four-level scale: “very easy”, “easy”, “difficult” and “very difficult”. For the rating, the score of each item is reduced to a binary score, the “very easy” and “easy” modalities scoring for 1 while “difficult” and “very difficult” for 0. The total score can then vary from 0 to 16. To facilitate interpretation, they can be classified into three literacy levels: less than or equal to 8 reflecting an inadequate level, from 9 to 12 reflecting a problematic level and strictly greater than 12, an adequate level.

The distribution of the three score levels will be described preoperatively and postoperatively in each arm.

Validated in French, this short scale of the “European Health Literacy Survey Questionnaire” (14) has acceptable psychometric qualities and allows a reduced administration time for participants, the latter having several questionnaires to complete at the same time as part of the study.

Effects on professionals

Qualitative evaluation of changes in practices following the integration of 3D models into the practice of the service.

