|                     | 
Secondary objectives :
 
 
1. To use qualitative studies to describe interactions between professionals and patients, specifying the situations in which exchanges take place and their environments.
 
2. To use qualitative studies to compare differences in discourse and the use of terms in the use of different tools during interactions between patients, professionals and family and friends.
 
3. To use a qualitative approach to study the use of the 3D-printed kidney model introduced during a medical information consultation right through to the post-operative visit.
 
4. To compare patient understanding of anatomy and surgical strategy according to the type of tool, personalised or generic, before and after the operation on the basis of questionnaires and interviews.
 
5. To compare the level of health literacy between the two groups and at different times (HLSEU-Q16: European Health Literacy Survey Questionnaire).
 
1. 6. To use qualitative studies to describe the changes perceived by professionals in patient care following the integration of the patient mediation tool.
 
                                                 |
| ASSESSMENT CRITERIA | 
MAIN JUDGING CRITERION :
 
Mixed criterion used to describe the patient experience based on the interviews. Observations and the three questionnaires used complete the qualitative data analyses. The patient experience will also be analysed in relation to the clinical and demographic data from the UroCCR database.
 
SECONDARY JUDGEMENT CRITERIA :
 
 
1. Conduct of interactions between professionals and patients: description of the conduct of interactions according to the model used, specifying the practice and the vocabulary and content of the discourse used.
 
2. Frequency of terms used in accordance with the use of the various tools during interactions.
 
3. Use of the 3D model during care: description of the life of the model throughout care (from the inclusion visit to the post-operative visit).
 
4. Level of understanding of renal anatomy and surgical issues.
 
5. Change in the mean score of the HLSEU-Q16 literacy questionnaire measured (health literacy).
 
1. 6. Effects on professionals: qualitative assessment of changes in practice following the integration of 3D models into the department's practice.
 
 |

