| Modeling virtual 3D-model (according to randomized arm)  |                            |                    | X               |                                |                      |            |                             |                  |
| Printing 3D-model (according to randomized arm)          |                            |                    | X               |                                |                      |            |                             |                  |
| Preoperative information according to randomized arm     |                            |                    |                 | X                              |                      |            |                             |                  |
| Surgery                                                  |                            |                    |                 |                                |                      | X          |                             |                  |
| ASSESSMENTS                                       |                            |                    |                 |                                |                      |            |                             |                  |
| HLSEU-Q16 questionnaire (health literacy)                |                            | X                  |                 |                                |                      |            | X                           |                  |
| Questionnaire (knowledge of disease and planned surgery) |                            | X                  |                 |                                | X                    |            |                             | X                |
| Questionnaire of satisfaction                            |                            |                    |                 |                                |                      |            |                             | X                |
| Semi-directive interview                                 |                            | X                  |                 |                                | X                    |            |                             | X                |
|                                                          |                            |                    |                 |                                |                      |            |                             |                  |

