### 7.4.2 EXCHANGE AND INFORMATION CONSULTATION (T2)

Patients are seen between 30 days and 7 days before the operation by a member of the surgical team. The purpose of this discussion time is to allow the patient to express their questions, share their doubts or misunderstandings in relation to their medical situation and the scheduled intervention. It may lead to explanations on anatomy and simple surgical strategies by the member of the surgical team participating in this interview.

The two interventional groups (Personalized 3D Printed Model Group and Generic 3D Printed Model Group) are presented with the model as a discussion support.

The explanations given to patients are not standardized within the framework of the study in order to be closer to usual practice.

The duration of this visit as well as the presence or absence of an accompanying person will be collected.

A member of the SHS research team may participate in the visit as an observer.

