### 9.3.4 ANALYSIS OF SECONDARY OBJECTIVES

The description of interactions between professionals and patients, specifying the terms used and their frequencies, will be carried out via the analysis and synthesis of the information collected via the observation notebooks. This analysis will make it possible to respond to secondary objectives 1 and 2. Additional elements concerning patient and entourage interactions may come from interviews with patients and will enrich the response to objective 2.

To respond to the third secondary objective, a synthesis of all the information collected as part of the observations but also from interviews with patients and professionals will make it possible to trace the use made of 3D models and to understand the users and the circumstances of use.

The evolution of the understanding of the disease and surgery will be studied by analyzing the content of the interviews and the questionnaire on understanding renal anatomy and surgical issues with a tablet on UroConnect. The content will be compared between the two groups.

A descriptive analysis of the distribution of scores obtained by patients for the HLS-EU16 literacy questionnaire will be carried out in each group for times 1 and 6. A comparison analysis between time 1 and time 6 will be carried out, for each group, by a paired Student test, after checking the homogeneity of variances, otherwise non-parametric tests will be used. Finally, the changes between the two groups (HLSEU-Q16 at time T6 - HLSEU-Q16 at time T1) will be compared by a Student test.

A second analysis will be carried out using the classification of the literacy score into three levels as indicated in section 4.2, the data will be described for each time and then a comparison between times will be carried out by a paired Chi-square test.

A thematic content analysis of the interviews conducted with professionals will be carried out.

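### The knowledge comparison for objective 4 is split at the model presentation in Protocol 3.2 but at the operation in 2.2, the synopsis and the abstract, and 9.3.4 does not say which between-arm contrast answers it

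*Protocol*

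**What the plan says.** Objective 4 concerns understanding of anatomy and surgical strategy.

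- **Section 2.2:** the arms are compared "according to the type of tool, personalised or generic, before and after the operation on the basis of questionnaires and interviews". The synopsis has the same objective in the same terms.
- **Abstract, secondary outcome 4:** the comparison is made "according to the type of tool (personalized vs generic 3D printed model) before and after the surgery (T1, T3 and T6"). It keeps surgery as the divide but lists three visits.
- **Section 3.2:** "These dimensions will be studied before and after the presentation of the model and compared according to the model used". The divide is now the showing of the model.
- **Section 9.3.4:** the evolution of understanding will be studied through interviews and the questionnaire, and then "The content will be compared between the two groups". No time pair or change score is named. The same section does fix T6 minus T1 for the HLSEU-Q16.

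The schedule in section 7.2 places the knowledge questionnaire at T1, T3 and T6. On T2, section 7.4.2 says: "Patients are seen between 30 days and 7 days before the operation by a member of the surgical team". Section 7.4.3 puts T3 between that consultation and surgery.

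**The concern.** One endpoint has two dividing events, and the middle one of its three measurements changes side between them. T3 is the first reading after the model has been shown and the last one before surgery. Under 3.2 it counts as after; under 2.2, the synopsis and the abstract it counts as before.

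Hypothesis 1 in section 1.2 is that the personalised model gives better understanding, and this questionnaire is the quantitative evidence for it, alongside the interviews. The model acts at T2. The T3 comparison therefore measures the immediate effect, and the T6 comparison measures what is left after surgery. These are different questions and can have different answers in the same data. If the choice between them is made once three time points are visible, a reader cannot tell which one was planned.

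**Working it through.** The Protocol states no figure to reproduce. Section 9.1 sets 60 patients, 30 per arm, without an effect size, SD or power.

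**Order of events (sections 7.2 to 7.5)**

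| Event | T1 | T2 | T3 | T4 | T6 |
|---|---|---|---|---|---|
| What happens | questionnaire | model shown | questionnaire | surgery | questionnaire |
| Side under 3.2 | before | divide | after | – | after |
| Side under 2.2, synopsis, abstract | before | – | before | divide | after |

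T1 and T6 keep their side. Only T3 moves.

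**What each between-arm contrast estimates.** Let D be the mean difference, personalised minus generic, at T3, and r the share of D still present at T6. The expected difference at T1 is 0, because allocation is random and section 7.3.3 withholds the result from the patient until T2. Then:

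- T3 − T1: D − 0 = D
- T6 − T1: rD − 0 = rD
- T6 − T3: rD − D = (r − 1)D
- T6 − mean(T1, T3): rD − D/2 = (r − 0.5)D
- arms compared at each visit: 0, D and rD

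Appendix 2 has 8 + 4 + 8 = 20 items. With an assumed D of 3 items:

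| r | T3 − T1 | T6 − T1 | T6 − T3 | T6 − mean(T1, T3) |
|---|---|---|---|---|
| 1 | +3 | +3 | 0 | +1.5 |
| 0.5 | +3 | +1.5 | −1.5 | 0 |
| 0.25 | +3 | +0.75 | −2.25 | −0.75 |

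The first two contrasts keep the sign of D for any r above 0, and they agree in size only when r = 1. The last two carry T3 in the baseline, so they remove all or half of the effect.

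**Precision of the T3 comparison.** Scale scores to SD 1 and let ρ be the correlation between visits. Assume an effect of 0.5 SD at T3, 30 per arm, and a two-sided 5% test.

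- Change score T3 − T1: SD = √(2(1 − ρ)).
- T3 adjusted for T1: residual SD = √(1 − ρ²).
- Noncentrality = (0.5 / SD) × √(30/2).

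At ρ = 0.5:

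- change: SD = 1.000, noncentrality 0.5 × 3.873 = 1.94, power about 48%
- adjusted: SD = √0.75 = 0.866, noncentrality 0.577 × 3.873 = 2.24, power about 59 to 60%

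At ρ = 0.7:

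- change: SD = √0.6 = 0.775, noncentrality 0.645 × 3.873 = 2.50, power about 69%
- adjusted: SD = √0.51 = 0.714, noncentrality 0.700 × 3.873 = 2.71, power about 75 to 76%

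An unadjusted test of T3 alone has SD 1 and power of about 48% whatever ρ is.

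**The two ordinary readings compared.** If half the effect is lost by T6, T6 − T1 targets 0.25 SD. At ρ = 0.5 the noncentrality is 0.25 × 3.873 = 0.97 and power is about 16%, against 48% for T3 − T1.

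**The case against.** The strongest reply is that the two wordings are compatible. In 2.2 the comparator is the type of tool, and the operation only marks the occasions. The abstract names those occasions, the schedule collects the questionnaire at exactly those visits, and T6 also follows the presentation of the model. The same data serve both wordings, and the exact contrast is ordinary material for a statistical analysis plan. The outcome is secondary in a mainly anthropological study, and objective 4 draws on interviews as well.

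Much of this stands. A reader might infer that the operation wording leads the trial to report no effect, or a reversed one, when the personalised model works. The documents do not support that. It requires T6 − T3, or T6 against T1 and T3 pooled, and no passage states either contrast. Nor is T3 − T1 the only contrast that isolates the model: with randomised arms, the T6 difference is a valid estimate of the effect at a later time. A false positive rate of about 12% from choosing freely among three contrasts includes the unstated T6 − T3, and nothing shows that the Protocol permits such a choice.

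On adjustment, section 9.2.1 foresees an adjusted analysis beside the unadjusted one, but for prognostic factors found unbalanced. It does not name the T1 knowledge score.

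What does not fall away is that the current text gives two divides for one endpoint. An analysis plan that follows one departs from the other. Listing T1, T3 and T6 does not say which comparison answers the objective.

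**Conclusion.** The inconsistency is real and limited. T3 changes side between 3.2 and the other three statements of objective 4, and 9.3.4 does not settle the contrast. The ordinary readings are each valid but estimate D at T3 and rD at T6, which differ unless the gain is fully kept. A T3 baseline would subtract the effect out; that is a possibility the wording leaves open, not something the Protocol plans.

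This should be corrected, because it is cheap and best done before results are seen. It does not threaten the main objective. D, r, the 0.5 SD effect and the correlations are all assumptions. The algebra holds for any D and r, but the power figures are illustrative only.

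**What to change.** Align section 2.2, the synopsis, the abstract, section 3.2 and section 9.3.4 on one statement:

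1. The comparison of the two models for objective 4 is the between-arm difference in knowledge score at T3, adjusted for the same patient's T1 score.
2. The T6 score, also adjusted for T1, is reported as a separately labelled between-arm comparison of retained understanding after surgery.
3. T3 is not used as a baseline.

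Keeping T6 as a between-arm comparison, not mere description, respects the Protocol's aim of covering the period before and after surgery and the whole care pathway. Adjusting for T1 replaces the unadjusted Student or Wilcoxon test of 9.2.5 for this endpoint and uses data already collected.

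The cost is wording in five places, with no new visit, patient or questionnaire. Section 3.2 speaks of several knowledge dimensions, so the statement should also say which score it applies to; this change does not by itself control error across dimensions.
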